### Sample size 

To account for between-cluster variability, sample size calculations incorporated the coefficient of variation between pharmacies (*k*) [25, 26]. Assuming each cluster enrolls 95 (accounting for 15% attrition) AGYW and that 30% of participants achieve the primary outcome of PrEP persistence at 10 months (31) in the standard pharmacy PrEP model arm (control arm) arm with a coefficient of variation between clinics (*k*) of 0.05, 10 clusters per arm will give 90% power to detect a 15% absolute difference in proportions and a two-sided test with *α* = 0.05. Typical (*k*) values are 0.15 to 0.5 for rare binary outcomes and 0 to 0.05 for non-rare outcomes [25, 26]. Assuming 15% attrition, will enroll a final sample of 1900 ANC attendees at 20 sites (95 women per site; 950 women per arm).

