### Recruitment 

AGYW who purchase a contraceptive method at a retail pharmacy study site will be recruited and enrolled. AGYW will be recruited into this trial following the purchase of contraception. Pharmacy staff will be aware of the study and asked to identify potentially eligible women at the point of contraceptive purchase. Pharmacy staff will explain the study to women who are potentially eligible and, if the woman expresses an interest in participating, will refer her to study staff. The study staff will then provide an in-depth explanation of the purpose and procedures of the study, in the language of the woman’s choosing, answer any questions the woman may have, and invite the woman to participate in the study. Participants will be informed that their participation is voluntary and that participation or nonparticipation in the study will in no way alter the nature of services that they receive at the pharmacy. If interested in participating, the study staff will screen the woman for eligibility, and, if eligible, the woman will provide written consent for their enrollment.

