## Assignment of interventions: allocation

### Sequence generation 

Following pharmacy provider training, the study randomized 20 pharmacies 1:1 to either receive (*n* = 10) or not receive (*n* = 10) a nurse navigator arm to support PrEP delivery for AGYW. The pharmacy-level cluster randomization will be conducted using restricted randomization based on AGYW volume (i.e., monthly number of purchases made by AGYW clients) stratified by sub-county. Following study protocol training at an in-person event with staff from all 20 pharmacies, pharmacy staff were asked to select a ball with a random study arm assignment from a bag within each of the 10 groups to build camaraderie and demonstrate transparency of the randomization process.

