### Concealment mechanism 

Since randomization occurred at the pharmacy level, it is impossible to blind study team members or participants to randomization assignments. However, procedures to minimize the influence of the unblinded nature of this study on outcomes are implemented. Randomization was only disclosed after all pharmacies were recruited and trained and signed agreements to participate in the study, following ethical approval. Ongoing data monitoring does not include information about study endpoints disaggregated by site or study arm. Only the study statistician will review data on study endpoints by study arm or facility.

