## Statistical methods

### Statistical methods for primary and secondary outcomes 

We will conduct an intention-to-treat analysis with the primary exposure of randomization arm (pharmacy-based PrEP delivery with nurse navigators vs. standard pharmacy-based PrEP delivery without nurse navigators) to test the hypotheses that incorporating nurse navigators within a pharmacy-based PrEP delivery model will improve PrEP initiation, persistence, and adherence among AGYW seeking contraception at retail pharmacies.

For analyses of our primary outcomes, we will use a log-binomial regression model to estimate relative risks and 95% CI. We will include any imbalanced baseline demographic, clinical, or behavioral characteristics between arms as independent variables in an adjusted model. If primary outcome data are missing or in cases of loss to follow-up, we will assume PrEP discontinuation/nonadherence to fit the most conservative models.

Secondary outcome analyses will include PrEP method selection, predictors of non-adherence, and STI incidence and cofactors. For data analysis approaches, we will use log-binomial regression with robust standard errors for the former two and Anderson-Gill survival analysis for the later. Exploratory analyses will include HIV incidence, quality of care, and contraceptive method mixed by randomization arms (Table 1). We will use survival analysis, generalized estimating equation models with logistic link, and robust standard errors and log binomial regression respectively.

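### The adjusted model takes covariates by observed baseline imbalance and does not name the sub-county and volume factors that restricted the randomization

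*Protocol article*

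**What the plan says.** Under Statistical methods for primary and secondary outcomes, the protocol article says of the three primary outcomes that "we will use a log-binomial regression model to estimate relative risks and 95% CI". The next sentence gives the covariate rule: "We will include any imbalanced baseline demographic, clinical, or behavioral characteristics between arms as independent variables in an adjusted model". It does not say how imbalance is judged, which variables are candidates, or whether the adjusted or the unadjusted model is primary.

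Under Sequence generation, allocation used "restricted randomization based on AGYW volume (i.e., monthly number of purchases made by AGYW clients) stratified by sub-county", and pharmacy staff were asked to "select a ball with a random study arm assignment from a bag within each of the 10 groups". Ten groups for 20 pharmacies at 1:1 implies pairs, if the groups are of equal size. No analysis section carries sub-county, volume or the groups into a model.

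Recruitment follows allocation, which is open: "Pharmacy staff will be aware of the study and asked to identify potentially eligible women at the point of contraceptive purchase". On access to results by arm, Concealment mechanism says: "Only the study statistician will review data on study endpoints by study arm or facility".

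**The concern.** Two features of the stated analysis pull in the wrong direction.

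First, a covariate earns its place in a trial model by predicting the outcome. Under this rule it enters because the arms happen to differ on it. A strong predictor that is balanced stays out, and an irrelevant variable that differs by chance goes in. Different readings of imbalanced give different covariate sets, and so several possible adjusted answers for each of three primary outcomes.

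Second, the factors that shaped the randomization are the obvious candidates for the model, and the rule is unlikely to reach them. Restriction on volume and sub-county balances them by design. They are also pharmacy-level attributes, while the rule speaks of demographic, clinical and behavioral characteristics.

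The recruitment process adds weight. Staff who know the arm identify potential participants, so case mix could differ between arms for reasons other than chance. The better protection is a prognostic list fixed in advance.

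**Working it through.** **Inputs from the protocol article.** 10 clusters per arm; 95 enrolled per cluster and 15% attrition, so about 81 retained (0.85 × 95); control persistence 30%; absolute difference 15 points; k = 0.05; two-sided α = 0.05; stated power 90% (all Sample size). 

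**Assumed, because the article does not give them.** Number of baseline variables tested and the 5% test level; baseline ICC; four sub-counties; share of between-pharmacy variance explained by sub-county and volume.

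**1. The plan's own power figure.** With V = [p0(1−p0) + p1(1−p1)]/n + k²(p0² + p1²), power = Φ(√[(c−1)(p1−p0)²/V] − 1.96).

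- n = 81: within = 0.4575/81 = 0.00565; between = 0.0025 × 0.2925 = 0.00073; V = 0.00638. Power = Φ(√(9 × 0.0225/0.00638) − 1.96) = Φ(3.67) = 99.99%.
- n = 95: 99.998%.

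The stated 90% does not reproduce. At n = 81 it needs V = 0.2025/10.507 = 0.01927, so k² = (0.01927 − 0.00565)/0.2925 = 0.0466 and k ≈ 0.22. That mismatch is a separate matter. It is the reason for showing results at both k = 0.05 and k ≈ 0.22.

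**2. How readily the rule flags variables by chance.** For ten independent variables tested at 5%, P(at least one flag) = 1 − 0.95^10 = 40%. If the tests treat women as independent, the design effect at ICC 0.01 is 1 + 94 × 0.01 = 1.94. The true per-test rate is then P(|Z| > 1.96/√1.94) = 0.16, and 1 − 0.84^10 ≈ 82%. At ICC 0.02 (design effect 2.88) it is 94%. Ten is not a large number here: the baseline data described under Plans for assessment and collection of outcomes span about nine domains.

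**3. What the randomization factors could buy at k = 0.05.** Between-pharmacy variance is 0.00073/0.00638 = 11% of the total. Explaining 30% or 50% of it cuts the standard error by 1 − √(1 − 0.3 × 0.1146) = 1.7% or 1 − √(1 − 0.5 × 0.1146) = 2.9%, before any loss of degrees of freedom.

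**4. Simulation that counts degrees of freedom.** Cluster-level linear model, 81 women per pharmacy, 20 pharmacies in 10 pairs, 6,000 runs. Residual df are 18 unadjusted, 14 with sub-county and volume, and 9 with all pairs. The entries are mean 95% CI half-widths for the risk difference at explained shares of 0 / 50% / 80%.

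| k | Unadjusted | Sub-county + volume | All 10 pairs |
|---|---|---|---|
| 0.05 | 0.0524 / 0.0522 / 0.0524 | 0.0532 / 0.0516 / 0.0509 | 0.0557 / 0.0539 / 0.0530 |
| 0.15 | 0.0720 / 0.0717 / 0.0718 | 0.0732 / 0.0633 / 0.0564 | 0.0767 / 0.0665 / 0.0594 |
| 0.22 | 0.0919 / 0.0911 / 0.0908 | 0.0936 / 0.0757 / 0.0624 | 0.0978 / 0.0797 / 0.0665 |

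- k = 0.05: adjusting for sub-county and volume ranges from 2% wider to 3% narrower. Pair effects are 1% to 6% wider than no adjustment.
- k = 0.15 to 0.22, with half or more of the variance explained: 12% to 31% narrower.
- In every row, pair effects are wider than sub-county plus volume.
- Type I error of the unadjusted analysis: 0.046 to 0.050 at k = 0.05. At k = 0.22 it falls to 0.026 (share 50%) and 0.007 (share 80%), which is conservative.

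**The case against.** The strongest reply is that the article is a condensed account. Under Interim analyses it refers to a statistical analysis plan, which is not shown and could add the randomization factors and a covariate list. That stands for the factors: a reader might infer that the analysis excludes them, but the article is only silent. It does not stand for the selection rule, which the article states outright and which a plan following it would inherit.

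Three stronger readings are tempting, and the document does not support them.

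- **That the analysis loses material precision.** At the protocol's own k it does not. Larger gains need a k that the article does not assume and an explained share that nobody has estimated. Where the factors do matter, omission widens the interval and lowers type I error. It does not bias the estimate.
- **That whoever picks the covariates already knows the results by arm.** The article reserves endpoint data by arm to the statistician. It does not say who applies the imbalance rule or when. Weekly reports on baseline characteristics, described under Adverse event reporting and harms, would allow imbalance to be judged without endpoints.
- **That the primary answer depends on this rule.** The article speaks of an adjusted model without ranking it. If the unadjusted estimate is primary, the rule governs only a supporting analysis.

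It can also be said that, with open recruitment after allocation, an observed imbalance may be real selection and worth examining. That is fair, and it is a reason to keep such a model as a labelled sensitivity analysis. The plan also mentions no significance tests, so the 5% level in the working is illustrative.

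**Conclusion.** The point holds for the selection rule. The article settles the covariates of a primary-outcome model by observed imbalance, with no list or criterion. That rule does not pick prognostic variables, is likely to flag some by chance (40% to 94% for at least one of ten, under the assumptions shown), and makes the adjusted answer depend on the data. The stated model also does not name sub-county or AGYW volume, and the rule would tend to pass over them.

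The precision argument is secondary: about 3% of interval width at most at k = 0.05 for explained shares up to 80%, and 12% to 31% only at k of 0.15 to 0.22 with half or more of the between-pharmacy variance explained. These figures rest on an assumed four sub-counties, assumed shares and a cluster-level linear model, not the planned log-binomial model. The case for change is therefore mainly prespecification.

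**What to change.** Replace the covariate sentence with a fixed specification along these lines:

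*The adjusted model for each primary outcome contains arm, sub-county, log monthly AGYW volume of the pharmacy, and age, marital status and contraceptive method at enrollment. The list is final before endpoints are reviewed by arm. The unadjusted estimate is reported alongside. A model that adds covariates because of observed imbalance is reported only as a sensitivity analysis and labelled as such.*

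- The three individual covariates are examples. The sponsor should choose a short list on prognostic grounds from what is already collected.
- Coarsen sub-county if needed, so that pharmacy-level terms use no more than 2 to 3 degrees of freedom. The number of sub-counties is not given.
- Do not fit fixed effects for all 10 pairs: they take 9 degrees of freedom and widen the interval at k = 0.05.
- State whether the adjusted or the unadjusted estimate is primary.

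The cost is a change of wording and a few pharmacy-level degrees of freedom. If the factors explain nothing, the interval is about 2% wider in the simulation, which spent four such degrees of freedom. No new data are needed.

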### Interim analyses 

Our data and safety monitoring plan is our strategy for oversight and monitoring to ensure the safety of participants and the validity and integrity of data from the study. We will convene an external advisory panel (EAP) to review study aims, statistical analysis plan, and protocol. At annual EAP meetings, enrollment, retention, and pooled outcomes will be reviewed. The EAP can recommend suspension or termination of the study due to serious concerns about participants’ safety, inadequate performance, scientific policy developments that impact the study, or inadequate enrollment rates.

### Methods for additional analyses (e.g., subgroup analyses) 

Subgroup analyses will involve data from all AGYW at the enrollment visit to evaluate the effect of STI testing on PrEP initiation. We will also evaluate the association between offering STI testing at PrEP initiation and time-to-discontinuation using Cox proportional hazards models. We will have sufficient power to detect differences in the frequency of PrEP persistence of 14% or 60% between AGYW offered and not offered STI testing, assuming a 2-sided test with alpha = 0.05 and 80% power (*β* = 0.20). All models will use robust standard errors.

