### Trial design 

This is a two-arm, unblinded, cluster-randomized controlled trial in which 20 retail pharmacies offering standard PrEP delivery are randomized 1:1 to either receive or not receive a nurse navigator to support PrEP delivery for AGYW.

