## Data collection and management

### Plans for assessment and collection of outcomes 

We will collect baseline data on demographic and behavioral characteristics, contraceptive history, education, marital status, income, relationship characteristics, HIV status and testing results, and clinical characteristics. At each visit, study staff will administer questionnaires to participants to assess sexual behavior, PrEP attitudes, use, and adherence. We will also measure IMB model-guided psychosocial moderating factors, including experience of IPV, symptoms of depression, socioeconomic status (SES), sexual and reproductive empowerment (SRE) and health, and PrEP use disclosure. We will assess SRE with the SRE-Kenya scale, which has been adapted and validated by our group for Kenyan AGYW. We will also capture PrEP-related side effects (e.g., nausea, headaches, dizziness) [27]. Fidelity will be monitored through QA/QC with direct observation of client-provider interactions using MEASURE Evaluation’s framework for monitoring quality of care in family planning services [28]. Hair samples (~ 50 strands) will be collected from all participants at every follow-up visit to objectively assess PrEP use and longitudinal analyses of PrEP use patterns.

HIV testing will be conducted at every visit per national guidelines. In a subset of four pharmacies, two from each study arm, we will conduct STI (for gonorrhea and chlamydia). The study utilizes the Cepheid Gene X-pert machine, a 4-module NAAT analyzer for real-time PCR testing of CT/NG and TV assays with expedited partner treatment for those with STI diagnoses to allow for analyses of STI incidence by arm.

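### The comparison of women offered and not offered STI testing is 4 versus 16 pharmacies, and the robust standard errors chosen for it do not hold a 5% error rate

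*Protocol article*

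**What the plan says.** All of the analysis text is in the protocol article under Methods for additional analyses. It gives two analyses of STI testing. The first is worded causally: "Subgroup analyses will involve data from all AGYW at the enrollment visit to evaluate the effect of STI testing on PrEP initiation". The second is not: "We will also evaluate the association between offering STI testing at PrEP initiation and time-to-discontinuation using Cox proportional hazards models".

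A power statement follows, claiming "sufficient power to detect differences in the frequency of PrEP persistence of 14% or 60" per cent between women offered and not offered testing, "assuming a 2-sided test with alpha = 0.05 and 80% power". The section closes with its one statement on variance: "All models will use robust standard errors". It names neither a clustering unit nor a reference distribution.

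How testing is allocated is given under Plans for assessment and collection of outcomes: "In a subset of four pharmacies, two from each study arm, we will conduct STI (for gonorrhea and chlamydia". How the four were chosen is not stated. Under Trial design, "20 retail pharmacies offering standard PrEP delivery are randomized 1:1 to either receive or not receive a nurse navigator"; Sequence generation likewise describes randomisation of the navigator only.

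**The concern.** STI testing is a feature of the pharmacy. A comparison that uses all participants therefore sets 4 pharmacies against 16, whatever the number of women. Robust (sandwich) standard errors are justified when clusters are many. With four clusters on one side, most of the variance of the difference comes from those four and is estimated on three degrees of freedom. The sandwich estimate is then too small on average and too unstable for a normal reference. If the robust errors treat women as independent, variation between pharmacies is left out altogether. Either way the confidence interval is too narrow and the p value too small.

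Two smaller faults sit in the same paragraph. The word effect is used for an exposure with no described randomisation, although the next sentence says association. And the power sentence concerns the proportion persisting, while the analyses named by STI offer are initiation and time to discontinuation. At stake is a report that STI testing changes PrEP use when the difference is chance, or a difference between those four pharmacies and the rest.

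**Working it through.** **The plan's own figure.** The article gives 14% or 60% as the detectable difference in persistence, without group sizes, a reference rate or a scale. The nearest inputs are in the Sample size section: 95 women per site and 30% persistence. These give 4 × 95 = 380 against 16 × 95 = 1520. At 80% power the detectable difference is about 2.80 × √(0.376 × 0.624/380 + 0.30 × 0.70/1520) = 2.80 × 0.0275 ≈ 0.077. With the design effect of 1.10 derived below, it is 0.077 × √1.10 ≈ 0.081. That is about 8 points, not 14. If 14 points were also a 60% relative difference, the reference rate would be 14/0.60 = 23.3%, not 30%. The figure cannot be reproduced from the article.

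**Case A: robust errors clustered by pharmacy, normal reference.** Take equal-sized pharmacies with variance σ² for a pharmacy mean.

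- True variance of the difference: σ²(1/4 + 1/16) = 0.3125σ².
- Expected sandwich variance: σ²(3/4² + 15/16²) = σ²(0.1875 + 0.0586) = 0.2461σ². With the usual factor 20/19 this is 0.2590σ².
- Ratio to the truth: 0.2590/0.3125 = 0.83, so the variance is about 17% too small on average.
- Effective degrees of freedom (Satterthwaite): 0.2461²/(3 × (1/16)² + 15 × (1/256)²) = 0.06056/0.01195 ≈ 5.1. A normal reference assumes infinitely many.

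Simulation under a true null puts the two faults together:

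| Method, 4 versus 16 pharmacies | Rejection of a true null, nominal 5% |
|---|---|
| Pharmacy-clustered robust error (factor 20/19), normal reference | about 12.5% |
| The same, beta-binomial data, 95 women per pharmacy, k = 0.05 | about 12.5–13% |
| The same robust error with 18 df, no bias correction | about 10.5% |
| Pooled t test on pharmacy summaries, 18 df | about 5.0% |

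**Case B: robust errors not clustered by pharmacy.** The article's k = 0.05 is converted by ρ = k²p/(1 − p). The design effect is 1 + 94ρ, and the true size of a nominal 5% test is 2 × [1 − Φ(1.96/√design effect)].

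| Outcome rate p | ρ | Design effect | True size |
|---|---|---|---|
| 30% (assumed control persistence) | 0.00107 | 1.10 | 6.2% |
| 60% (illustrative) | 0.00375 | 1.35 | 9.2% |
| 85% (initiation in the pilot, Background) | 0.01417 | 2.33 | 19.9% |

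Beta-binomial simulation at 30% and 85% gave 6.2% and 20.1%. Larger k makes Case B worse. Case A changes little with k, because its fault lies in the number of clusters.

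**The case against.** The strongest reply is that this is a journal article. The clustering unit, the reference distribution and any small-sample correction are commonly left to the statistical analysis plan, which the article mentions and which is not shown. That stands in part. The rates above are conditional on how the robust errors are implemented, and a plan that prescribes a suitable small-sample method would meet the point. What remains is that the article fixes a method, and neither ordinary implementation of it holds 5% with four pharmacies on one side.

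A second reply is that these are additional analyses, outside the objectives and Table 1, and that effect appears once, beside association. This is fair, and it keeps the wording point small. The article's silence also does not prove that the four pharmacies were chosen non-randomly. It shows only that no randomisation of STI testing is described.

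A third reply is that persistence is the binary counterpart of time to discontinuation: stopping before 10 months counts as non-persistent, so powering on the proportion is a common simplification. This too is fair. Persistence is also a primary outcome compared by randomised arm, so it would be wrong to call it an outcome that the trial does not analyse. The gap is that no persistence analysis by STI offer is named.

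**Conclusion.** The point holds as one about the variance method. For 4 versus 16 pharmacies, the stated robust standard errors give about 12.5–13% false rejections per test when clustered by pharmacy with a normal reference. Unclustered, at k = 0.05, they give about 6% at a 30% outcome rate and about 20% at 85%. These figures assume roughly equal pharmacies of 95 women and no true difference. They were worked out for proportions and are taken as a guide for the Cox model. They measure chance alone: any systematic difference between the four pharmacies and the rest is confounding, which they do not cover. The causal wording and the mismatched power sentence are lesser, textual faults.

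A reader might go further and infer an uncontrolled family of confirmatory tests, each at 5%, with a missing split of alpha. The article does not support that. The section is headed as additional analyses, 0.05 appears only inside the power sentence, and a split of alpha among such analyses can be left to the analysis plan. Nor does it support the inference that a false finding on PrEP uptake would drive guidelines: the Discussion ties guideline relevance to STI incidence.

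**What to change.** In Methods for additional analyses:

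1. Replace the sentence on robust standard errors, for the STI-testing comparisons, with pharmacy-level inference and a small-sample reference. One option is a t test or regression on pharmacy summaries, with about 18 degrees of freedom or fewer; adjusting for nurse-navigator arm leaves 20 − 3 = 17. The other is bias-corrected cluster-robust errors with degrees of freedom matched to the design. For the unadjusted contrast these are (3/12 + 15/240)²/(3/12² + 15/240²) = 0.0977/0.0211 ≈ 4.6. Substituting 18 degrees of freedom without bias correction is not enough, since it still rejects about 10.5% of the time.
2. Adjust these comparisons for nurse-navigator arm.
3. Describe the comparison as an exploratory, non-randomised association between offering STI testing and PrEP outcomes, in place of a subgroup analysis of an effect.
4. Attach the power statement to an outcome analysed by STI offer, with its group sizes, reference rate and scale, or delete it.

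The cost is a few sentences and a small change of analysis code, with no extra participants or procedures. The price is a wider interval and a weaker claim for STI testing. Against Case A, the pharmacy-level interval is roughly (2.11/1.96) × √(0.3125/0.2590) ≈ 1.18 times as wide.

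### STI testing is offered in only 4 of 20 pharmacies, too few exposed clusters for robust standard errors in their usual forms to hold a two-sided 5% error rate

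*Protocol article*

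**What the plan says.** The Trial design section gives the number of clusters: "20 retail pharmacies offering standard PrEP delivery are randomized 1:1". Under Plans for assessment and collection of outcomes, STI testing is confined to some of them: "In a subset of four pharmacies, two from each study arm, we will conduct STI".

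Methods for additional analyses then asks two questions about STI testing. The first concerns initiation: "Subgroup analyses will involve data from all AGYW at the enrollment visit to evaluate the effect of STI testing on PrEP initiation". The second relates "offering STI testing at PrEP initiation and time-to-discontinuation using Cox proportional hazards models". The section claims adequate power, "assuming a 2-sided test with alpha = 0.05 and 80% power", and ends with one sentence on inference for all of these models: "All models will use robust standard errors". It does not state the clustering unit, a small-sample correction or a reference distribution. The article does not say how the four pharmacies were selected.

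**The concern.** Whether a woman is offered STI testing depends on the pharmacy she attends. The information about the contrast therefore comes mainly from the number of pharmacies on each side, and one side has four.

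Robust standard errors can be read in two ways here. If they are computed by individual, ordinary variation between pharmacies can be mistaken for an effect of testing. If they are clustered by pharmacy, the usual sandwich with a normal reference assumes many clusters in each exposure group. With four, the variance is biased downward and is itself poorly estimated.

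At stake is the credibility of a p-value or interval for STI testing. A chance difference between four pharmacies and the rest could be reported as testing raising or lowering PrEP initiation or persistence, with an error rate well above the stated 5%.

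**Working it through.** **Inputs.** 20 pharmacies (Trial design); 4 with STI testing, 2 per arm (Plans for assessment and collection of outcomes); 95 women per pharmacy, 30% persistence and k=0.05 (Sample size); 85% initiation in the pilot (Background and rationale). Values of k above 0.05 are assumptions.

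**The plan's own figure.** The only figure for this analysis is a detectable difference: "differences in the frequency of PrEP persistence of 14% or 60% between AGYW offered and not offered STI testing". With 4 × 95 = 380 against 16 × 95 = 1520 women, a base rate of 30% and no clustering, the detectable difference is (1.96 + 0.84) × √(0.377×0.623/380 + 0.30×0.70/1520) = 2.80 × 0.0275 = 7.7 points. About 14 points appears only with roughly 190 against 190, a split the article does not state. The 60% could not be reproduced. This is a separate matter, and nothing below depends on it.

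**Pharmacy-clustered errors, by approximation.** Let σ² be the variance of a pharmacy-level result, with equal cluster sizes and no arm term.

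- True variance of the contrast: σ²(1/4 + 1/16) = 0.3125σ².
- Expected value of the uncorrected sandwich (CR0): σ²(3/16 + 15/256) = 0.2461σ², a ratio of 0.7875. With the factor 20/19 (CR1) the ratio is 0.829.
- Satterthwaite degrees of freedom: (1/4 + 1/16)² / [(1/4)²/3 + (1/16)²/15] = 0.09766/0.02109 = 4.63.
- CR0 with 1.96: effective cut-off 1.96 × √0.7875 = 1.74; P(|t| > 1.74) on 4.63 df = 14.7%.
- CR1 with 1.96: cut-off 1.78, giving 13.9%.
- CR1 with t(19): cut-off 1.91, giving 12.0%.

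**Pharmacy-clustered errors, by simulation under a true null.** The binary outcome used 100,000 beta-binomial replicates per setting; the Cox model used 6,000 replicates per setting with gamma frailty.

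| Method | Rejection at nominal 5% |
|---|---|
| CR0 or CR1, normal reference, log relative risk, rates 30-85% | 12.3-14.1% |
| Cox, clustered, normal reference | 13.0-13.8% |
| CR1 with t(19), equal sizes | 10.4-11.3% |
| CR1 with t(19), unequal sizes (CV about 0.5) | 11.8-12.7% |
| CR0, arm-adjusted, normal reference | 14.4-15.8% |
| CR2, Satterthwaite df about 4.6, arm-adjusted | about 4-5% |

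The clustered results hardly move with k, because they come from the number of exposed pharmacies.

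**Individual-level robust errors.** Here k matters. The intracluster correlation is k²p/(1−p), the design effect is 1 + 94 × ICC, and the rejection rate is 2[1 − Φ(1.96/√DE)].

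- p=0.30, k=0.05: ICC 0.00107, DE 1.10, rejection 6.2%.
- p=0.85, k=0.05: ICC 0.0142, DE 2.33, rejection about 20%.
- p=0.30, k=0.15 (assumed): ICC 0.0096, DE 1.91, rejection 15.6%.
- p=0.30, k=0.30 (assumed): ICC 0.0386, DE 4.63, rejection 36%.

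**The case against.** The strongest objection is that the plan is incomplete here rather than wrong. It never commits to a normal reference. A condensed article may leave the clustering unit and small-sample correction to an analysis plan that is not shown. A bias-reduced sandwich with suitable degrees of freedom is also a robust standard error, and it holds its level. This stands in part: 12-14% is the consequence of one common implementation, not a stated property of the plan. But the section is not silent. It gives one inference rule for every model, and the usual forms of that rule fail for this contrast to some degree.

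Several stronger readings are tempting and are not supported:

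- **That the article itself describes a 4 v 16 comparison.** It does not. The split follows from joining two sections, although the article offers no other account of who is offered testing.
- **That ignoring clustering is always worse than clustering badly.** At the protocol's own 30% and k=0.05, individual-level errors reject only about 6%. The larger figures need either 85%, from a pilot in two pharmacies with nurse navigators, or k above the 0 to 0.05 that the Sample size section calls typical for non-rare outcomes.
- **That screening guidelines hang on this test.** The guideline statement in the Discussion concerns STI incidence, not the effect of testing on PrEP use.
- **That any pharmacy-level or permutation test would cure the problem.** An unweighted regression of pharmacy log-proportions with t(17) rejected 4.9-5.0% at a 30% rate with equal sizes and equal variability. It rejected 11% when the exposed pharmacies were assumed to average 50 women against 106, and 12% when k was assumed to be 0.22 against 0.10. Permutation needs the four pharmacies to have been chosen at random.

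**Conclusion.** The concern holds in a limited form. For a contrast resting on 4 exposed pharmacies, the usual pharmacy-clustered sandwich has a true error rate of about 12-14% with a normal reference and about 10-12% with t(19), against a nominal 5%. Individual-level robust errors range from about 6% to 20% at k=0.05, depending on the outcome rate, and go higher at larger assumed k.

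The conclusion assumes that exposure is 4 v 16, as inferred from the two sections, and that no small-sample correction beyond the usual defaults is applied. An unseen analysis plan could already contain one. The matter is confined to an additional analysis that is not listed in Table 1; the primary comparison of 10 with 10 pharmacies is untouched. It should be settled before the STI-testing results are analysed.

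**What to change.** In Methods for additional analyses, replace the general sentence, for the STI-testing models only, with standard errors clustered by pharmacy, a bias-reduced (CR2-type) correction, Satterthwaite degrees of freedom (about 4-5) and study arm as a covariate. A pharmacy-level t analysis is acceptable only if the four pharmacies resemble the others in size and variability. A within-arm permutation test (45 × 45 = 2025 allocations) is acceptable only if the four were chosen at random.

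State how the four were chosen. Unless it was at random, describe the initiation result as an association, as the section already does for time to discontinuation.

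This is a wording change with no new data. The cost is a wider interval: at 4.63 df the multiplier is 2.63, so relative to the uncorrected clustered interval the width grows by about 2.63/(1.96 × √0.7875) = 1.5 times (equal sizes, no arm term).
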